## 4.4 Schedule and Ethical Consideration

The study on asthenopia in individuals with presbyopia aims to begin enrollment immediately after receiving ethics approval from the Hong Kong Polytechnic University's Ethics Committee. This approach guarantees uniform ethical standards and participant protection measures.

## 4.5 Study Methodology

### 4.5.1 Study Procedure

- Eligibility: The research team will conduct visual acuity tests, slit lamp examinations, accommodation function examinations, and fundus examinations on the subjects to verify their eligibility for the study. Then informed consent will be obtained from the eligible subjects. Sociodemographic information and general health history will also be recorded.
- Asthenopia measurement: The asthenopia questionnaire scores will be derived from the Computer Vision Syndrome Questionnaire (CVS-Q), a widely recognized tool for assessing subjective symptoms of asthenopia. Change in CFF and other objective asthenopia indicators (e.g., eye movement, pupil parameters, and blink patterns) will be measured by a non-invasive eye tracker at 2 weeks and 1 month compared to baseline.
- Accommodation function: AA, AF, BCC, NRA, PRA, and AC/A ratio will be evaluated by optometrists at baseline, 2 weeks, and 1 month.
- Near visual ability: The NAVQ scores will be derived from the Near Activity Visual Questionnaire, a widely recognized tool for assessing near-vision functioning in presbyopia. HNVA was assessed at 40 cm using a near LogMAR chart under the participant’s habitual near correction. ADD was determined as the minimum additional lens power required to achieve best near visual acuity under full distance correction.
- Visual acuity: Best-corrected distance visual acuity (BCDVA) and best-corrected near visual acuity (BCNVA) at 40 cm will be measured at baseline, 2 weeks, and 1 month.
- Cognitive tests: Cognition function will be measured by EEG and the MoCA at baseline, 2 weeks, and 1month.
- Emotional states: Self-reported emotional states will be assessed by the PANAS-X at baseline, 2 weeks, and 1 month.
- Fundus Examinations: At baseline, 2 weeks and 1 month, participants will undergo non-invasive fundus examinations using Optical Coherence Tomography (VG200) and Laser Speckle Flowgraphy (LSFG-NAVI).

The data collected for the baseline visit and the follow-up visits are showed in Table 1.

Table 1. Time and Events Schedule for Study Procedures

|  | **Visit 1 (baseline examinations)** | **Visit 2 (2 weeks)** | **Visit 3 (1month)** |
| --- | --- | --- | --- |
| Pre-screening criteria | √ |  |  |
| Informed consent | √ |  |  |
| Non-cycloplegic refraction | √ |  |  |
| Slit lamp examination | √ |  |  |
| BCDVA | √ | √ | √ |
| BCNVA | √ | √ | √ |
| HNVA | √ | √ | √ |
| EEG | √ | √ | √ |
| MoCA scale | √ | √ | √ |
| Accommodation amplitude | √ | √ | √ |
| Facility of accommodation | √ | √ | √ |
| Accommodative response (BCC) | √ | √ | √ |
| Relative accommodation (NRA and PRA) | √ | √ | √ |
| AC/A ratio | √ | √ | √ |
| CVS-Q questionnaire | √ | √ | √ |
| NAVQ questionnaire | √ | √ | √ |
| CFF test | √ | √ | √ |
| Eye tracker test | √ | √ | √ |
| PANAS-X questionnaire | √ | √ | √ |
| Optical Coherence Tomography | √ | √ | √ |
| Laser Speckle Flowgraphy | √ | √ | √ |

### 4.5.2 Data Anonymity and Security

The information supplied by participants constitutes the research data. Any research data that can be used to identify participants is classified as personal data. Personal data does not include data where the identity has been removed (anonymous data). We will minimize our use of personal data in the study as much as possible. The researchers and their team, supervisors, collaborators will have access to personal and research data solely for study purposes. Responsible members of The Hong Kong Polytechnic University may be given access for monitoring and/or audit of the research.

All information related to the participants will remain confidential and be securely encrypted and stored with de-identification to ensure privacy. Confidentiality is mandated by agreements for all parties involved. The information collected will be kept until 5 years after project completion. The Hong Kong Polytechnic University takes reasonable precautions to prevent the loss, misappropriation, unauthorized access or destruction of the information that participants provide.

# **5. Participants Safety and Withdrawal**

## 5.1 Risk Management and Safety

The primary risk of the intervention is related to the low-level red-light therapy. The RLRL therapy device (Eyerising International Pty Ltd, Melbourne, Australia) is a semi-conductor laser product, with a power of 0.29 mW for a 4-mm pupil. It holds CE certification in the European Union, MHS registration in Malaysia, TGA approval in Australia, MHRA approval in the UK, medical device registration in Turkey, Medsafe registration in New Zealand, and a certificate from the National Medical Products Administration (NMPA) in China for myopia treatment. The manufacturer is certified under the ISO 13485 quality management system for medical device production. The device is widely available and commonly used for amblyopia treatment. Studies on the efficacy of RLRL for juvenile myopia control have been conducted in China, with no reported ocular complications or adverse effects in clinical trials.

Common side effects of the light therapy device include flash blindness, short-term glare, and afterimages, which typically resolve after a few minutes of eye closure. The examinations in this study are standard clinical procedures widely used in practice and research, posing minimal to no risk.

Adherence to task guidelines will be closely supervised, with active monitoring for adverse events. Any incidents will be promptly documented and addressed. Safety data, including discomfort, side effects, or health concerns, will be systematically collected and reviewed. Participants will be fully informed of potential risks and safety protocols.

## 5.2 Handling of Withdrawals

Study participation will be terminated by an investigator for the following reasons:

1. Any severe adverse event, such as a sudden loss of vision greater than two lines or the development of a central visual field scotoma.
2. The participant meets an exclusion criterion (either newly developed or previously unidentified) that precludes further involvement.
3. Any other reason deemed appropriate by the investigator.
4. New safety information necessitates halting the study.

Participants may withdraw from the study at any time upon request. Those who withdraw will be asked about their reasons and whether permission is granted to use data collected prior to withdrawal. If permission is denied, all associated data will be deleted from the system.

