## 4.2 Randomization and Masking

Eligible participants will be randomly assigned in a 1:1 ratio to either the intervention group or the control group, using a computer-generated randomization sequence. The intervention group will undergo RLRL therapy, while the control group will use a sham device, which operates at only 10% of the active device’s power. The light power through a 4-mm pupil is 0.29 mW for the RLRL device and 0.03 mW for the sham device. This therapy will be administered using a desktop semiconductor therapy device developed by Eyerising International Pty Ltd, based in Sydney, Australia.

Group assignments were concealed using opaque, sealed, and sequentially numbered envelopes. Each participant was assigned a number according to the order of enrollment, and the corresponding envelope was opened at the time of allocation to determine group assignment. Participants, optometrists, ophthalmologists, clinical examiners, and statisticians were all masked to the treatment allocation. However, if a participant experiences severe adverse reactions, the blinding may be lifted after the investigator determines that unblinding is necessary.

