# **6. Statistical Methods**

## 6.1 Sample Size Estimation & Justification

The primary outcome was the change in Computer Vision Syndrome Questionnaire (CVS-Q) score at the 31-day follow-up visit. Due to the absence of prior randomized trials on RLRL therapy for presbyopia, the sample size estimation was informed by feasibility-based assumptions. We assumed a standardized mean difference of Cohen’s d = 0.80. Using a two-sided alpha of 0.05 and 80% power, calculations performed in G*Power 3.1 indicated a requirement of 26 participants per group (total n = 52). Allowing for a 15% loss to follow-up, the final target enrollment was 31 participants per group, totaling 62.

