## 6.3 Statistical Methods to Be Undertaken

The normality of continuous variables will be assessed using the Kolmogorov–Smirnov test. Categorical variables will be summarized as counts and percentages (n [%]), and continuous variables as means ± standard deviations (SD). For comparisons of demographic or baseline characteristics between groups, independent samples t-tests will be used where assumptions are met. If data are not normally distributed or are ordinal, non-parametric tests such as the Mann–Whitney U test (for independent samples) and the Wilcoxon signed-rank test (for paired samples) will be applied. Outcomes were analyzed using both intention-to-treat (including all randomized participants) and per-protocol (including participants who completed both follow-up visits) approaches. To assess treatment effects over time, general linear mixed-effects models will be employed to account for repeated measures across multiple follow-up time points.

All statistical tests will be two-tailed with a significance level of α=0.05. Effect sizes, accompanied by 95% confidence intervals, will be reported to quantify the practical significance of the findings.

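### Section 5.2 ends study participation without separating it from stopping the device, so the day-31 CVS-Q may be missing for participants whom the ITT analysis in section 6.3 is meant to include

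*Protocol*

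**What the plan says.** Protocol section 5.2 opens its list with "Study participation will be terminated by an investigator for the following reasons". The four reasons are a severe adverse event, an exclusion criterion (arising after entry or discovered late) that rules out continuing, a discretionary investigator's reason, and new safety information that halts the study. What ends is participation in the study; stopping the device is not mentioned separately. Table 1 in section 4.5.1 schedules visits at baseline, 2 weeks and 1 month, and none specifically for a participant who has been terminated.

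The same section then turns to participants who leave at their own request. They are asked whether data already collected may be used, and "If permission is denied, all associated data will be deleted from the system". Section 5.3 says that dropouts are not replaced.

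Section 6.3 promises an analysis by "intention-to-treat (including all randomized participants", alongside a per-protocol analysis of those who completed both follow-up visits, with mixed-effects models for the repeated measurements. Section 2.3 puts the primary outcome, change in CVS-Q, at day 31. Section 6.1 states "Allowing for a 15% loss to follow-up, the final target enrollment was 31 participants per group, totaling 62".

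**The concern.** An intention-to-treat analysis needs the outcome of every randomised participant, whether or not the device was still in use. Section 5.2, as written, ends measurement along with treatment. A participant terminated before day 31 has no primary outcome, and one terminated before the 2-week visit has only a baseline value. At day 31 the observed data behind the ITT and per-protocol analyses then become nearly the same, so the first is a weak check on the second. Terminating someone for an exclusion criterion discovered late is also a post-randomisation exclusion.

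The people affected are unlikely to be a random sample. The protocol itself describes a route by which losses could be linked to arm:

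- Section 4.2 gives light power of 0.29 mW for the active device and 0.03 mW for sham.
- Section 5.1 lists afterimages among the common side effects.
- Section 3.3 makes an afterimage lasting more than 6 minutes an exclusion criterion.
- Section 5.2 lets a newly arising exclusion criterion end participation.

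Masking does not close this route, because the trigger would be a physical effect of the light and not knowledge of the allocation. If such losses fall mainly on the active arm and those participants would have done less well, the estimated benefit is too favourable.

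**Working it through.** **1. The plan's own sample size.** Inputs from section 6.1: "We assumed a standardized mean difference of Cohen’s d = 0.80"; "Using a two-sided alpha of 0.05 and 80% power"; "requirement of 26 participants per group (total n = 52". Section 4.2 gives 1:1 allocation. The exact two-sample t-test (noncentral t) has power 0.791 at 25 per group and 0.807 at 26, so 26 is right. Allowing for 15% loss, 26 / 0.85 = 30.6, rounded up to 31 per group and 62 in total. The stated figures reproduce.

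**2. Does unequal loss threaten power?** The allowance covers 62 − 52 = 10 losses. Exact power at d = 0.80, with splits by arm that are my assumption:

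| Lost (active / sham) | Analysed | Power |
|---|---|---|
| 5 / 5 | 26 / 26 | 0.807 |
| 7 / 3 | 24 / 28 | 0.805 |
| 8 / 2 | 23 / 29 | 0.802 |
| 10 / 0 | 21 / 31 | 0.793 |

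Power barely moves. The 15% allowance deals with precision and does nothing about bias.

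**3. Size of a possible bias.** The exposure ratio is 0.29 / 0.03 = 9.7, about tenfold, but the protocol gives no termination rates by arm, so the inputs here are assumptions. Let k of 31 active participants and no sham participants be lost. Let the remaining active participants have a mean benefit of 0.80 SD over sham, and let the lost ones have had mean m. In a simple comparison of means:

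- with the lost participants absent, the estimate is 0.80;
- with everyone followed, the estimate is [(31 − k) × 0.80 + k × m] / 31;
- the difference is (k / 31) × (0.80 − m).

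For k = 3:

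- m = 0: (28 × 0.80 + 0) / 31 = 22.4 / 31 = 0.72, a difference of 0.08 SD;
- m = −1: (22.4 − 3) / 31 = 19.4 / 31 = 0.63, a difference of 0.17 SD.

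Over a range of k:

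| k of 31 | Followed estimate, m = 0 | Difference | Followed estimate, m = −1 | Difference |
|---|---|---|---|---|
| 1 | 0.77 | 0.03 | 0.74 | 0.06 |
| 2 | 0.75 | 0.05 | 0.68 | 0.12 |
| 3 | 0.72 | 0.08 | 0.63 | 0.17 |
| 5 | 0.67 | 0.13 | 0.51 | 0.29 |

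With a milder gap of 0.5 to 1.0 SD between lost and remaining participants, the difference for k = 3 is 3/31 × 0.5 = 0.05 to 3/31 × 1.0 = 0.10 SD.

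These are differences in simple means. The planned mixed model was not fitted. It could reduce the difference for participants with a 2-week value, to the extent that this value predicts day 31.

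**The case against.** The strongest reply is that this is an ordinary missing-data problem. Terminated participants keep their baseline data and any 2-week data, and these can enter the mixed model in the randomised arm. Section 6.1 already expects 15% loss, and a statistical analysis plan that is not shown may set out how missing values are handled. This stands in part: the ITT analysis is weakened, not ruled out. But no analysis plan can recover a day-31 questionnaire that a conduct rule prevented from being collected.

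Four stronger readings are tempting, and the protocol does not support them.

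- *That the ITT analysis cannot be delivered.* It is impossible only for someone who withdraws and refuses use of earlier data. Others contribute what was measured.
- *That losses will depend on arm.* No rates are given. Section 5.1 says that the common side effects usually pass within minutes, and it reports no ocular complications or adverse effects in juvenile myopia trials, though that is another population. The adverse-event reason requires a severe event, and an exclusion criterion counts only if it rules out continuing. Masking limits arm-related discretion, and a study-wide halt affects both arms. The risk is plausible, but its size is unknown.
- *That deletion removes the safety record of those harmed.* The deletion sentence follows the one on withdrawal at the participant's request, so on its natural reading it does not cover people terminated by the investigator. The narrower gap is real: a voluntary withdrawer's adverse-event record could be lost, although section 5.1 promises systematic collection of safety data.
- *That the expected bias is 0.08 to 0.17 SD.* That range rests on an assumed 3-to-0 split and assumed outcomes.

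**Conclusion.** The concern holds in a conditional form. Section 5.2 does not separate stopping the intervention from leaving follow-up. Applied as written, it leaves the ITT analysis in section 6.3 possibly incomplete at the primary time point and reliant on data being missing at random. Those losses may be related to arm.

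The stated sample size is correct, and power stays between 0.79 and 0.81 however 10 losses divide. The issue is bias. In the illustration with 3 active and no sham losses, the estimate is 0.80 against 0.72 or 0.63 with full follow-up. That is 0.08 / 0.80 = 10% to 0.17 / 0.80 = 21% of the planned effect. It depends on the assumed number lost, their assumed outcomes and a simple comparison of means, and the planned model could make it smaller. This should be fixed: the conflict lies in the text, the data cannot be recovered afterwards, and the change is cheap. It does not by itself invalidate the design.

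**What to change.** Reconcile section 5.2 with section 6.3:

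- State that, for the first three reasons, ending the intervention does not by itself end follow-up. Participants who agree, and for whom the investigator has no safety objection, are asked to attend whichever of the 2-week and day-31 visits remain, at least for the CVS-Q. They are analysed in their randomised arm.
- Exempt a study-wide halt (the fourth reason) and withdrawal of consent.
- Leave the clinical reasons for stopping as they are.
- For withdrawers who refuse use of their data, report the number by arm. Where ethics rules allow, keep the allocated arm and the adverse-event record. Whether they allow it is for the ethics committee.

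The cost is a change of protocol and consent wording and a few extra attendances at visits already scheduled. The planned sample size does not change.

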## 5.3 Replacement

Drop out will not be replaced.

## 5.4 Protocol Waivers or Deviations Justification

Protocol deviation is not allowed.

# **6. Statistical Methods**

## 6.1 Sample Size Estimation & Justification

The primary outcome was the change in Computer Vision Syndrome Questionnaire (CVS-Q) score at the 31-day follow-up visit. Due to the absence of prior randomized trials on RLRL therapy for presbyopia, the sample size estimation was informed by feasibility-based assumptions. We assumed a standardized mean difference of Cohen’s d = 0.80. Using a two-sided alpha of 0.05 and 80% power, calculations performed in G*Power 3.1 indicated a requirement of 26 participants per group (total n = 52). Allowing for a 15% loss to follow-up, the final target enrollment was 31 participants per group, totaling 62.

## 6.2 Power Calculations

Please refer to 6.1 Sample Size Estimation & Justification.

## 6.3 Statistical Methods to Be Undertaken

The normality of continuous variables will be assessed using the Kolmogorov–Smirnov test. Categorical variables will be summarized as counts and percentages (n [%]), and continuous variables as means ± standard deviations (SD). For comparisons of demographic or baseline characteristics between groups, independent samples t-tests will be used where assumptions are met. If data are not normally distributed or are ordinal, non-parametric tests such as the Mann–Whitney U test (for independent samples) and the Wilcoxon signed-rank test (for paired samples) will be applied. Outcomes were analyzed using both intention-to-treat (including all randomized participants) and per-protocol (including participants who completed both follow-up visits) approaches. To assess treatment effects over time, general linear mixed-effects models will be employed to account for repeated measures across multiple follow-up time points.

All statistical tests will be two-tailed with a significance level of α=0.05. Effect sizes, accompanied by 95% confidence intervals, will be reported to quantify the practical significance of the findings.

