# **4. Study Design**

## 4.1 Study Type and Design

This prospective, randomized controlled study will enroll individuals aged 40 years or older who have asthenopia and presbyopia. The study aims to evaluate the effectiveness of RLRL therapy in reducing asthenopia and presbyopia symptoms, as well as its impact on cognitive function and emotional well-being.

Eligible participants will be randomly assigned in a 1:1 ratio to either the intervention group or the control group. Each participant in the intervention group will be provided an RLRL therapy device, which they are required to use twice daily for 3 minutes per session, with a minimum interval of 4 hours between sessions, 7 days a week for one month. Participants in the control group will receive a sham device, following the same usage schedule. The study will evaluate changes in asthenopia questionnaire scores, near visual ability, other objective asthenopia indicators, accommodation function, cognitive function, and emotional states at 2 weeks and 1 month compared to baseline.

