## 4.3 Intervention Compliance Monitoring

Each participant will receive an RLRL therapy device or a sham device and must log in with their unique account details before each treatment session. The device is connected to a centralized system via the internet, allowing for remote monitoring of treatment data and compliance. Two staff members from the project team will review treatment compliance and usage statistics weekly.

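### The per-protocol set is defined by visit attendance alone, so it is a completers set and cannot show the effect under protocol use of the device

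*Protocol*

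**What the plan says.** Section 6.3 names two analysis approaches. The first is all-inclusive: "Outcomes were analyzed using both intention-to-treat (including all randomized participants". The second is "per-protocol (including participants who completed both follow-up visits) approaches". That parenthesis is the whole per-protocol definition. The two follow-up visits are those at 2 weeks and 1 month (section 4.5.1, Table 1).

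Three other places bear on it:

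- **Section 4.1** sets what participants must do. The device is to be used "twice daily for 3 minutes per session, with a minimum interval of 4 hours between sessions, 7 days a week for one month", and the sham group follows the same schedule.
- **Section 4.3** describes the record of use. Participants log in before each session, and the system is described as "allowing for remote monitoring of treatment data and compliance". It adds: "Two staff members from the project team will review treatment compliance and usage statistics weekly". It gives no adherence threshold and no link to an analysis set.
- **Section 6.1** fixes the endpoint: "The primary outcome was the change in Computer Vision Syndrome Questionnaire (CVS-Q) score at the 31-day follow-up visit". The 2-week measurement is not part of it.

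**The concern.** A per-protocol analysis is meant to show the effect in people who received the treatment as planned. Here the treatment is self-administered at home, so the main way to depart from the plan is not to use the device. A definition that looks only at clinic attendance misses that departure and penalises a different one.

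If the results are reported under this label, readers will take the second analysis as the effect with adequate use. Similar results in the two analyses would look like reassurance about adherence when adherence had played no part in the selection. A difference between them would reflect who attended, not who was treated. The plan would then contain no estimate of the effect under protocol use, although the data for one are being collected.

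**Working it through.** **1. The plan's own figure.** Inputs from section 6.1: d = 0.80, two-sided alpha 0.05, power 80%, 15% loss. The noncentral t calculation for two independent means gives power 0.791 with 25 per group and 0.807 with 26, so 26 per group is right. Inflating, 26 / 0.85 = 30.6, rounded up to 31 per group, 62 in total. The sample size reproduces and is not in question here.

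**2. The rule applied to each type of participant.**

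| Device use | 2-week visit | Day-31 CVS-Q | In the set under 6.3? | Fits a per-protocol purpose? |
|---|---|---|---|---|
| As scheduled | attended | yes | in | yes |
| Hardly any | attended | yes | in | no: did not follow section 4.1 |
| As scheduled | missed | yes | out | no: treated as planned, primary outcome available |
| Any | any | no | out | yes: no primary outcome |

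Rows 2 and 3 are the two misclassifications. No other section removes row 2. Section 5.2 gives no adherence reason for ending participation, only a general investigator-discretion item. Section 5.4 disallows deviations but does not say how they are classified for analysis. Nor does the model require row 3 to be excluded: section 6.3 plans mixed-effects models, which can use a participant who has one of the two follow-up measurements.

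**3. Size of the exclusion (row 3).** The protocol gives no rate for missing only the 2-week visit, so 5% and 10% are assumptions. The right base is participants expected to have day-31 data, not those enrolled: 31 x 0.85 = 26.35, about 26 per arm.

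- 5%: 26 x 0.05 = 1.3 per arm
- 10%: 26 x 0.10 = 2.6 per arm

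**4. Size of the retention (row 2).** No rate of non-use is given either. Suppose a share q of attenders in the active arm do not use the device. Assume also that non-users gain nothing, that the SD is unchanged, and that 0.80 is the effect with full use. The expected d in this set is then 0.80 x (1 - q):

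- q = 10%: 0.80 x 0.90 = 0.72
- q = 20%: 0.80 x 0.80 = 0.64
- q = 30%: 0.80 x 0.70 = 0.56

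The same dilution would occur in the intention-to-treat analysis, where it is intended. The figures show only that the per-protocol set as defined does not remove it. They do not predict this trial's result.

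**The case against.** **Visit completion can be part of a per-protocol definition.** The 2-week visit is scheduled, CVS-Q is collected there, and the models use repeated measures. Missing it is a departure from the schedule. This stands as far as it goes: attendance may be one component, but it cannot be the only one in a trial of a home-use device. For an endpoint at day 31, it is also a weak reason to discard an adherent participant's primary outcome.

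**A separate SAP may add a use criterion.** It may. The protocol, however, does not leave the definition open. It states one, and that statement is what is criticised.

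**Selecting on logged use has its own bias.** This stands. Use is observed after randomisation and may differ between the active device and a sham running at a tenth of its power. It is a reason to keep the redefined set supportive, not a defence of a label with no use criterion behind it.

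**Stronger readings that the protocol does not support.** A reader might infer that, because 6.3 names two analyses without ranking them, success could be claimed on whichever is favourable. No section permits that. Intention-to-treat is listed first, and the ranking is something a SAP commonly sets. A reader might also take 0.56 to 0.72 as the effect this trial will show. Those values rest on non-use rates that the protocol does not give and on reading 0.80 as a full-use effect, whereas section 6.1 describes its assumptions as feasibility-based.

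**Conclusion.** The point holds in a limited form. The set that 6.3 calls per-protocol is a visit-completers set. It errs in both directions, retaining attenders who hardly used the device and excluding adherent participants who have the primary outcome. It would coincide with a true per-protocol set only if every attender used the device adequately and no adherent participant missed the 2-week visit alone.

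The number misclassified cannot be determined from the protocol. The 1.3 to 2.6 per arm is conditional on an assumed 5% to 10% missing only the 2-week visit. Participants excluded in this way remain in the intention-to-treat analysis, so their data are not lost to the trial. The fault affects one of two analyses and should be corrected, but it does not threaten the intention-to-treat result or the sample size.

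**What to change.** Replace the parenthesis in section 6.3 with a definition along these lines:

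> The per-protocol set comprises randomised participants with a day-31 CVS-Q, no major eligibility violation, and logged device use at or above a threshold fixed by the sponsor before unmasking. Attendance at the 2-week visit is not required for the day-31 primary outcome. This analysis is supportive to the intention-to-treat analysis.

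The threshold is for the sponsor to set, and none is proposed here. If the attendance-based set is still wanted, keep it under the name completers.

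The cost is one or two sentences and no new data collection, since section 4.3 already provides for monitoring of use. The redefined set may be smaller than the present one, by an amount that cannot be predicted without adherence data. Because it is selected on behaviour after randomisation that may differ between arms, it should be read only as supportive. Reporting logged use by arm beside it would let readers judge that risk.

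### Section 6.3 does not tie its mixed model to the day-31 CVS-Q change that is the primary outcome, and does not state adjustment for baseline CVS-Q

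*Protocol*

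**What the plan says.** Section 6.1, in line with section 2.3, fixes the outcome at one visit: "The primary outcome was the change in Computer Vision Syndrome Questionnaire (CVS-Q) score at the 31-day follow-up visit". The sample size follows from it: "We assumed a standardized mean difference of Cohen’s d = 0.80", then "Using a two-sided alpha of 0.05 and 80% power", giving 26 per group, and finally "Allowing for a 15% loss to follow-up, the final target enrollment was 31 participants per group, totaling 62".

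Table 1 in section 4.5.1 schedules the CVS-Q at baseline, 2 weeks and 1 month. Section 4.1 says that changes from baseline will be evaluated at both follow-up visits.

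Section 6.3 gives a normality test, rank-based alternatives and two analysis sets. For baseline data it says: "For comparisons of demographic or baseline characteristics between groups, independent samples t-tests will be used where assumptions are met". For the outcome model it says: "To assess treatment effects over time, general linear mixed-effects models will be employed to account for repeated measures across multiple follow-up time points". It does not state the response variable, the covariates, a group-by-visit term, or which estimate decides the primary outcome.

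**The concern.** The primary outcome and the sample size concern a single visit, while the only outcome model described spans all follow-up visits. Several analyses fit that description: the arm difference at day 31, an overall group effect across the two follow-ups, and either of these with or without baseline CVS-Q in the model. They differ in two ways that matter.

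- **What is estimated.** An overall group effect mixes the 2-week and day-31 effects, whereas the primary outcome is the day-31 effect alone.
- **How precisely.** With about 26 evaluable participants per arm, leaving the baseline score out of the model gives up precision that the collected data could supply at no cost.

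**Working it through.** **Inputs from the protocol.** From 6.1: d = 0.80, two-sided alpha 0.05, 80% power, 26 per group, 15% loss, 31 per group. From 4.2: 1:1 allocation. The protocol does not say which SD d is scaled on; it is read here as the SD of the change, because the primary outcome is a change.

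**Assumed inputs.** Equal SDs at the visits compared; baseline to day-31 correlation r from 0.3 to 0.8; correlation c between the 2-week and day-31 changes of 0.5 or 0.7. None of these is in the protocol.

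**1. The plan's own figure.** For a two-sample t-test the noncentrality is d × √(n/2) = 0.80 × √13 = 2.88, on 50 degrees of freedom. Power is 0.8075 at 26 per group and 0.7915 at 25, so 26 is right. Then 26 / 0.85 = 30.6, which rounds up to 31. Both figures reproduce, and they rest on a comparison without baseline adjustment.

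**2. Baseline adjustment.** With common SD σ, the variance of a change is 2σ²(1 − r), and the residual variance given baseline is σ²(1 − r²). The ratio is (1 − r²) / [2(1 − r)] = (1 + r)/2. The effective d is 0.80 / √ratio, and one degree of freedom is lost (49 instead of 50).

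| r | Variance ratio | Effective d | Power at 26 per arm | Evaluable n per arm for 80% power |
|---|---|---|---|---|
| unadjusted | 1 | 0.80 | 0.807 | 26 |
| 0.3 | 0.65 | 0.99 | 0.939 | 17 |
| 0.5 | 0.75 | 0.92 | 0.904 | 20 |
| 0.7 | 0.85 | 0.87 | 0.866 | 22 |
| 0.8 | 0.90 | 0.84 | 0.846 | 24 |

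If d were instead scaled on the SD of a single score, the direction would be the same: power goes from 0.667 to 0.842 at r = 0.3, from 0.807 to 0.904 at r = 0.5, and from 0.955 to 0.977 at r = 0.7.

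**3. An overall effect over both visits.** Let the day-31 effect be 0.80 SD and the 2-week effect f × 0.80. The average is 0.80(1 + f)/2 and its SD is √((1 + c)/2). For f = 0.5 and c = 0.5 this is 0.60 / 0.866 = 0.693.

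| f | Averaged effect | Power at 26 per arm, c = 0.5 | Power at 26 per arm, c = 0.7 |
|---|---|---|---|
| 0 | 0.40 | 0.372 | 0.335 |
| 0.5 | 0.60 | 0.688 | 0.634 |
| 0.75 | 0.70 | 0.815 | 0.766 |
| 1 | 0.80 | 0.904 | 0.866 |

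The averaged effect equals the day-31 effect only at f = 1.

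**The case against.** The strongest reply is that section 6.3 is silent rather than wrong. Model terms and covariates are commonly left to the SAP, which is not shown. A mixed model with an arm-by-visit term, a day-31 contrast and baseline CVS-Q fits the present wording. The day-31 time point is already fixed in 2.3 and 6.1. Section 4.1 speaks of the two follow-ups separately, so a visit-specific reading is at least as natural as an averaged one.

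Much of this stands, and it rules out three stronger readings.

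- A reader might infer that the plan analyses change without adjustment, because the baseline sentence in 6.3 mentions only between-group tests. The text does not exclude adjustment, and baseline values also enter the outcomes, which are defined as changes.
- A reader might infer that the two visits will be averaged. No section proposes this. The second table shows what would follow if an overall effect were tested, under assumed values of f and c; it does not describe the plan.
- A reader might infer that the trial is undersized or its test invalid. The 26 and 31 per group reproduce. Under randomisation an unadjusted comparison of change is valid, and it reaches the stated 80% power on the plan's own assumption.

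What the reply does not remove is that the protocol's only analysis section never connects its outcome model to the single-visit primary outcome, and does not say which test decides that outcome.

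**Conclusion.** The point holds as a gap in specification and a missed gain in precision, not as an error in the sample size or the validity of the test. Section 6.3 should be tied to the day-31 CVS-Q change and should state baseline adjustment.

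If change would otherwise be compared unadjusted, adjustment cuts the variance by 35% to 10% and raises power at 26 per arm from 81% to between 94% and 85%, for r from 0.3 to 0.8. This rests on equal SDs, on d being in units of the SD of change, and on an assumed range for r. The gain is smaller the higher r is.

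The cost of testing an overall effect instead cannot be fixed from the protocol, because it depends on the unknown 2-week effect. If that effect were half the day-31 effect, power would be about 63% to 69%; if the two were equal, nothing would be lost.

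**What to change.** Add to section 6.3, before unmasked data are seen:

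> The primary analysis is a linear mixed model for CVS-Q with categorical visit, arm-by-visit interaction and adjustment for baseline CVS-Q (as a covariate, or as part of the response with equal arm means at baseline). The primary estimate is the arm difference at day 31, tested once at two-sided 0.05.

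One of the two forms of baseline adjustment should be chosen and named. Continuous secondary outcomes can be adjusted for their own baseline values in the same way. If an SAP already fixes these terms, 6.3 need only say the same.

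The cost is two sentences of text. It needs no new data, visits or participants, and the target of 62 can stay as it is.
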